## Abstract

**Background:**

Poor physical performance and protein-energy wasting (PEW) are health issues of major concern in haemodialysis patients. The conventional haemodialysis (CHD) regime, three times per week 3–5 h, is subject of discussion because of high morbidity and mortality rates. When patients switch from CHD to longer dialysis sessions, i.e. nocturnal haemodialysis (NHD), improvement in protein intake and increase in body weight is seen. However, it is unclear whether physical performance and more important aspects of PEW, such as body composition, improve as well. Therefore, the aim of this study is to investigate whether physical performance improves and PEW decreases, when patients switch from CHD to NHD. A second aim is to assess the influence of NHD on the biomarkers fibroblast growth factor-23 and sclerostin which are thought to be associated with malnutrition and mortality in patients on haemodialysis.

**Methods:**

This study is a prospective multicentre cohort study with an inclusion aim of 50 patients: 25 patients in a control group (three times per week, 3–5 h CHD) and 25 patients in a nocturnal group (three times per week, 7–9 h NHD). Primary outcome is change in physical performance, measured by the Short Physical Performance Battery. Additional measurements are a 6-min walk test, handgrip strength, a physical activity questionnaire and physical activity monitoring. The secondary outcome of the study is PEW, which will be evaluated by body weight, dual-energy X-ray absorptiometry, bio-electrical impedance spectroscopy, mid-upper arm muscle circumference, subjective global assessment, visual analogue scale for appetite and dietary records. Laboratory measurements including fibroblast growth factor-23 and sclerostin, and quality of life assessed with the Kidney Disease Quality of Life-Short Form are also studied. In every patient, four repeated measurements will be performed during one year of follow-up.

**Discussion:**

This study will investigate whether physical performance improves and PEW decreases when patients switch from CHD to NHD, compared to a control group who continue treatment with CHD. Strengths of this study are the comparison with a conventional haemodialysis cohort, and the broad variety of objective measurements combined with patient-reported outcomes of physical performance and PEW.

**Trial registration:**

NTR4715, Netherlands Trial Register. Registered 30 July 2014.

## Background

Patients with end-stage renal disease (ESRD) are usually treated with a conventional haemodialysis (CHD) regimen, regularly prescribed as 3–4 times per week, 3–5 h haemodialysis sessions. However, prevalence rates of morbidity and mortality remain high, mainly due to cardiovascular complications [1–3]. Therefore, this routine of treatment is being questioned recently [3, 4].

Previous studies suggest that a twice as long haemodialysis treatment, applied as nocturnal haemodialysis (NHD), home or in-center, improves several clinical outcomes compared to CHD [5–8]. For example, improvements are found regarding hypertension and volume control, left ventricular mass, phosphate clearance, hospitalization rates, need for erythropoiesis stimulating agents and antihypertensive medications and survival [9–13]. Apart from cardiovascular complications, poor physical performance and protein-energy wasting (PEW) are risk factors of major concern in ESRD patients and contribute to this high morbidity and mortality [5–8]. Whether physical performance improves after a patient switches to NHD is unclear. Protein intake and body weight, parameters of PEW [14], seem to improve during NHD [15–17]. However, other aspects of PEW, such as muscle mass and mid-upper arm muscle circumference (MUAMC), are scarcely investigated.

Several biomarkers have been identified as risk factors for mortality in ESRD patients. Some of them are associated with bone remodelling and could be influenced by changes in physical activity and body mass. Fibroblast growth factor-23 (FGF-23) is a phosphaturic hormone produced in the osteocytes and is found to be increased in haemodialysis patients [18, 19]. FGF-23 may be associated with low body mass index (BMI) and malnutrition [20, 21]. The protein sclerostin is an important regulator of mineralization both in bone and vasculature. Sclerostin levels increase during progression of kidney disease and in patients on dialysis; however, it is not known whether this is the result of increased sclerostin production or decreased excretion. Studies reporting on associations between sclerostin levels and survival show contradictory results [22–25]. High levels of sclerostin seem associated with higher bone mass and might also have a relation with BMI and body composition [26]. It is of interest to evaluate possible changes in FGF-23 and sclerostin concentrations between ESRD patients who switch from CHD to NHD compared to ESRD patients who remain treated with CHD.

Here, we describe the general design and methodological issues of this study. This study will examine the effects of NHD compared to CHD on multiple intermediate outcome parameters of physical performance and PEW, and on the biomarkers FGF-23 and sclerostin.

## Methods

### Study design

This study is designed as a multicentre prospective cohort study. The NHD group will consist of patients who switch from CHD (2–4 times a week, 3–5 h) to in-centre NHD (2–4 times a week, 7–9 h). The control group will consist of patients who are treated with CHD and continue their treatment. The study protocol is in accordance with the Declaration of Helsinki and has been approved by the Medical Ethics Committee of VU University Medical Centre (VUmc).

### Study population

#### Recruitment of the study population

Patients in the NHD group will be recruited from Diapriva Dialysis Centre Amsterdam, the Netherlands. If a patient qualifies to switch from CHD to NHD depends primarily on the preference of the patient for NHD. Some medical conditions, such as instable angina pectoris, recent acute coronary syndrome, recent epileptic insult and aggressive behaviour are reasons to exclude a patient from NHD. This decision is made by a patient’s nephrologist. The control group will be recruited from VUmc, Diapriva and Spaarne Hospital Hoofddorp, the Netherlands. Patients will be approached by the investigator to inform them about the study and receive written information. Within two weeks patients will be approached by the executive research-dietician to ask for their willingness to participate. The patients who are not interested in NHD because of personal preferences, will be approached for participation in the control group. Patients who are rejected to participate the nocturnal program because of medical reasons, will not be asked to participate in the control group in order to avoid inclusion bias.

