A limitation of this study is a possible negative influence of this extensive battery testing on the willingness to participate to this study: the chronic dialysis population has already the burden of a time consuming dialysis treatment combined with numerous medical appointments. For the NHD patients we expect this to be of minimal influence, because they will be motivated to observe their own progression in physical performance and nutritional status when switching to another dialysis treatment. More difficulties could arise during the recruitment of the control patients, because improvements during the year regarding their physical performance status will probably not be realized. To overcome this barrier, we want to perform as much of the assessments during dialysis, also providing patients some kind of distraction from dialysis. Not all assessments will be feasible to perform during a dialysis treatment, namely the SPPB, BIS and 6MWT. Therefore, these tests will be assessed after a patient has finished the dialysis treatment. This could be another reason for control patients to be reluctant to participate. However, the assessments are easy and quick to perform, so we will emphasize this during recruitment and thereby expect the chance of missing data to be minimized. For the NHD group all tests will be performed after their dialysis treatment, because it will be infeasible to perform these tests during NHD.

Another limitation is the lack of randomization. However, comparing different dialysis modalities is hardly possible by randomization, because patients do not want to participate in such trials. Even large study consortia do not succeed in obtaining large enough patient numbers in NHD trials [13]. To avoid differences in both groups, we will not include patients in the control group that are excluded from NHD due to medical reasons. However, there might be a difference in patients who are motivated to perform NHD in comparison to patients who do not want this treatment, i.e. selection bias. In practice we notice that reasons not to perform NHD are often social reasons, e.g. having kids or a partner and not wanting to be away during the night. However, in order to minimize the effect of bias on the study results, we will correct the results for relevant confounding factors.

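### The medical safeguard on the control group bars only patients already rejected for NHD, and NHD patients come from one of three control centres, so the stated aim of avoiding inclusion bias is only partly met

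*Protocol article*

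**What the plan says.** All of the following is in the protocol article, under Recruitment of the study population unless another section is named.

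- **NHD source:** "Patients in the NHD group will be recruited from Diapriva Dialysis Centre Amsterdam, the Netherlands".
- **Control source:** "The control group will be recruited from VUmc, Diapriva and Spaarne Hospital Hoofddorp, the Netherlands".
- **Entry to NHD:** "If a patient qualifies to switch from CHD to NHD depends primarily on the preference of the patient for NHD".
- **Medical bar:** an open-ended list that starts with unstable angina and goes on: "recent acute coronary syndrome, recent epileptic insult and aggressive behaviour are reasons to exclude a patient from NHD". On who decides: "This decision is made by a patient’s nephrologist".
- **Entry to the control group:** "The patients who are not interested in NHD because of personal preferences, will be approached for participation in the control group". Patients whom the nocturnal programme turned down for medical reasons are not asked, and the stated purpose is to prevent inclusion bias.
- **Common exclusions (Inclusion and exclusion criteria):** these apply to both groups. They include unstable angina, myocardial infarction in the previous three months, severe pulmonary disease, dementia, a life expectancy under 12 months and non-adherence to dialysis.
- **Discussion:** to keep the groups alike, "we will not include patients in the control group that are excluded from NHD due to medical reasons". It then concedes possible selection bias from motivation and promises correction for relevant confounders.
- **Statistical analyses:** gender, age and dialysis vintage are given as examples of adjustment variables.

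**The concern.** The two groups reach the study by different doors. An NHD patient has wanted NHD and has not been stopped by the nephrologist on medical grounds. A control has not wanted NHD, and the text describes no point at which the nephrologist considers whether that patient could have had it. The bar on medically rejected patients catches someone who sought NHD and was refused. As worded, it does not catch someone with the same condition who never sought it.

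Separately, two of the three control centres are not named as sources of NHD patients. For controls at those centres, any difference in case mix or local care between centres coincides with the difference in dialysis regimen.

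The comparison of SPPB change between groups is the purpose of the study, and the protocol relies on this control rule to keep medical differences out of it. Both features are settled at recruitment. A later analysis plan can add covariates, but it cannot supply suitability decisions that were never recorded or Diapriva controls who were never enrolled.

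**Working it through.** **1. NHD exclusion reasons set against the common exclusions**

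| Reason against NHD (Recruitment) | Covered for controls by the common exclusions? |
|---|---|
| Unstable angina | Yes |
| Recent acute coronary syndrome | Partly: unstable angina, and infarction within 3 months |
| Recent epileptic insult | Not listed |
| Aggressive behaviour | Not listed |
| Other reasons (the list is open-ended) | Unknown |

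Of the four named reasons, one is covered, one is partly covered and two are not covered. The gap is real but narrower than the recruitment text alone suggests.

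**2. Overlap of centre and group**

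NHD: Diapriva only. Controls: Diapriva, VUmc and Spaarne, with no stated number per centre. If the 25 controls split evenly (an assumption), 25/3 ≈ 8 come from Diapriva and about 17, or two thirds, from the other two centres. Only the Diapriva controls allow an NHD-versus-CHD comparison within a centre.

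**3. The plan's own sample size, as the yardstick**

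Inputs from Statistical power: a 10% difference in SPPB, alpha 0.05, power 80%, SD 1.2 to 1.5. I read 10% as 1.2 points of the 12-point scale and alpha as two-sided.

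n per group = 2 × (1.96 + 0.84)² × SD² / 1.2²

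- SD 1.2: 15.7, so 16
- SD 1.5: 24.5, so 25

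This reproduces the stated 16 to 25 per group. The sample size is not in dispute.

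**4. What an imbalance could do (assumed values only)**

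Let f be the share of controls who would have been judged unsuitable, counted after the common exclusions, and d their extra SPPB loss over the year. The document gives neither. The shift in the group difference is b = f × d.

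With 25 per group, SE = SD × √(2/25), which is 0.339 at SD 1.2 and 0.424 at SD 1.5. With no true effect, the chance of a significant result is Φ(b/SE − 1.96) + Φ(−b/SE − 1.96).

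| f | d | b (points) | b / 1.2 | Error, SD 1.2 | Error, SD 1.5 |
|---|---|---|---|---|---|
| 10% | 0.5 | 0.05 | 4% | 5.2% | 5.2% |
| 10% | 1.0 | 0.10 | 8% | 6.0% | 5.6% |
| 20% | 1.0 | 0.20 | 17% | 9.1% | 7.6% |
| 20% | 2.0 | 0.40 | 33% | 21.8% | 15.6% |
| 30% | 2.0 | 0.60 | 50% | 42.4% | 29.3% |

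The two-sided error is the same whichever sign b has. A shift against NHD would instead hide a true benefit. If f is near zero, so is the effect.

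**5. Precision of a Diapriva-only comparison**

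With 25 NHD patients and 8 controls, SE = SD × √(1/25 + 1/8) = SD × 0.406, which is 0.487 at SD 1.2 and 0.609 at SD 1.5. Approximate power for 1.2 points is Φ(1.2/SE − 1.96), or 69% and 50%. The SE is 0.406/0.283 = 1.44 times that of the full comparison.

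**The case against.** Three stronger readings are tempting, and the document supports none of them.

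- *Medical fitness is judged only in patients who ask for NHD.* A reader might infer this from the primacy of preference and from the word used for rejected patients. The article gives no order of screening and does not say that uninterested patients go unassessed. The Discussion sentence, "we will not include patients in the control group that are excluded from NHD due to medical reasons", is broader and could take in anyone with a medical reason against NHD. What can be said is that no such assessment of controls is described.
- *The plan claims its controls are NHD-eligible.* It does not. It says medically rejected patients are left out, states an aim, and admits selection bias.
- *Controls will be sicker and decline faster, so NHD will look better.* The common exclusions already remove many patients likely to decline. Nothing in the document links epileptic insult or aggressive behaviour to loss of SPPB points. The Discussion says refusals are often for social reasons such as family life, which does not describe a sicker group.

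On centre, the list of confounders is open and an article may leave the full list to an analysis plan, so the absence of centre from that list is not itself a fault. Centre effects are also limited: one research-dietician role performs all tests, results are compared with baseline, and Diapriva supplies some controls.

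These points narrow the concern. What stands is that the safeguard's wording does not reach every control, that the common exclusions do not fill the whole gap, and that the overlap of centre and group comes from recruitment rather than from the choice of covariates. Comparison with baseline deals with differences in starting level, not with different rates of change. The disclosed selection bias concerns motivation, not centre.

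**Conclusion.** The point holds in limited form. As written, the control rule only partly meets its stated aim, because it acts on rejection from the programme and no NHD-suitability decision is described for uninterested patients at any of the three centres. The uncovered reasons are recent epileptic insult, aggressive behaviour, acute coronary syndromes outside the listed terms, and whatever else the open list includes. Centre is partly confounded with exposure, and this is not disclosed.

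The document does not allow the size or sign of any bias to be derived. The range in the working rests entirely on assumed shares and assumed extra decline, and shows only that the effect could be trivial or could matter against a 1.2-point target. This is a worthwhile, inexpensive improvement in recruitment and does not show that the comparison is invalid.

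**What to change.** 1. For every control candidate at all three centres, have the treating nephrologist record the same NHD-suitability decision, on the sponsor's existing criteria, as for NHD candidates. Enrol only those judged suitable. If this is already done, state it under Recruitment of the study population.
2. Pre-specify a sensitivity analysis of the SPPB outcome restricted to patients from Diapriva, and disclose the overlap of centre and group in the Discussion next to the selection bias from motivation.

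**Cost:** one yes/no item per control candidate, slightly slower control recruitment, and one extra analysis. With about 8 Diapriva controls, the restricted estimate would have roughly 50 to 70% power for 1.2 points, so it can support the main result but cannot settle the question. Its precision would improve if more controls came from Diapriva.

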#### Inclusion and exclusion criteria

Inclusion criteria for this study are: (1) age ≥18 years, (2) haemodialysis or hemodiafiltration treatment during ≥3 months, with stable haemodialysis regarding weight and blood pressure and absence of infection, (3) written informed consent and (4) ability to understand the study protocol. Patients will be excluded when suffering from: (1) dementia, (2) instable angina pectoris, (3) myocardial infarction in the last 3 months, (4) severe pulmonary disease, (5) a life expectancy of less than 12 months, (6) haemodialysis treatment incompliance, i.e. non-adherence to dialysis regimen, or (7) when they have a planned renal transplantation within 12 months.

### Outcome parameters

The Short Physical Performance Battery (SPPB) is the primary outcome parameter. Secondary outcome parameters are PEW, FGF-23 and sclerostin. Primary and secondary outcome parameters will be measured with a variety of tests, which are listed below (Table 1). All tests will be performed by the executive research-dietician. Baseline parameters will be assessed in duplicate with a 2- to 8-week interval, and after three, six and twelve months of follow-up. The duplicate baseline measurements are done to rule out a possible “learning effect” of the physical performance tests, in this way improving the objectiveness of the results. The mean of the two baseline measurements will be used for analyses. After the baseline measurements the NHD group will switch from CHD to NHD.

**Table 1 Tab1:** Assessments of physical performance and protein-energy wasting

Assessments	Baseline 1	Baseline 2	Months 3	Months 6	Months 12
Physical performance					
Short physical performance battery	x	x	x	x	x
6- min walk test (m)	x	x	x	x	x
Handgrip strength (kg)	x	x	x	x	x
Physical activity questionnaire	x	x	x	x	x
Physical activity monitor	x	x	x	x	x
PEW					
Body weight (kg) and body mass index (kg/m^2^)	x	x	x	x	x
Dual-Energy X-ray Absorptiometry	-	x	-	-	x
Bioelectrical impedance spectroscopy	x	x	x	x	x
Mid-upper arm muscle circumference (cm)	x	x	x	x	x
Subjective global assessment (score 1–7)	x	x	x	x	x
Dietary intake	-	x	-	-	x
Visual Analogue Scale appetite (cm)	x	x	x	x	x
Other					
Laboratory measurements (e.g. albumin, C-reactive protein)	x	x	x	x	x
FGF-23 and sclerostin	-	x	-	x	x
Quality of life (KDQOL-SF)	x	x	x	x	x
Sleeping behaviour questionnaire	x	x	x	x	x

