## Discussion

This study has several strengths. First of all, it has a prospective design and will include incident NHD patients. The results of NHD will be compared with baseline values, as well as with results of a control group, to account for changes over time and a possible learning effect of certain tests.

Second, physical performance and PEW will be measured using a wide range of objective measurements, combined with patient-reported outcomes. A combination of assessments in both ways will provide the most complete assessment of these outcomes. We expect a broad range of physical conditions in this population, due to e.g. various ages, weights and medical conditions. However, with all of these different tests, patients with marginal physical conditions will not have to be excluded. Also, a strength is the assessment of body composition measured with BIS as well as with a DXA scan which will provide comprehensive information regarding body composition. To our knowledge there are no previous studies investigating physical performance and PEW with this combination of different assessments.

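### Averaging the two baselines leaves half of any practice gain in within-group change on the performance tests, although the duplicate was meant to rule that gain out

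*Protocol article*

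**What the plan says.** The Protocol article, Outcome parameters, sets the schedule: "Baseline parameters will be assessed in duplicate with a 2- to 8-week interval, and after three, six and twelve months of follow-up". It gives the reason for the duplicate: "The duplicate baseline measurements are done to rule out a possible “learning effect” of the physical performance tests". The next sentence fixes how the pair is used: "The mean of the two baseline measurements will be used for analyses". Both tests precede the change of treatment: "After the baseline measurements the NHD group will switch from CHD to NHD".

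The Abstract defines the primary endpoint as a change: "Primary outcome is change in physical performance, measured by the Short Physical Performance Battery". The Discussion announces two comparisons, "The results of NHD will be compared with baseline values, as well as with results of a control group", and gives the purpose in the same sentence: "to account for changes over time and a possible learning effect of certain tests". The section Statistical analyses names a linear mixed model with adjustment for confounders. It does not say how baseline enters the model, and it gives no correction for practice.

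**The concern.** The stated purpose and the stated rule do not fit together. A familiarisation test removes practice from the reference value only if its result is kept out of that value. Here the unpractised first score makes up half of the baseline, while every follow-up test is done by a patient who has already performed the test twice. A gain that is only practice then appears as improvement from baseline.

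At stake is any statement that NHD patients improved on their own baseline in SPPB, six-minute walk distance or handgrip strength. Such a statement would be biased towards benefit, and the duplicate baseline would seem to have excluded that bias.

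**Working it through.** **Inputs from the document.** SPPB range 0 to 12 (Short Physical Performance Battery); difference of 10%, SD 1.2 to 1.5, alpha 0.05, power 80%, 25 per group (Statistical power); two baselines before the switch, then months 3, 6 and 12 (Outcome parameters, Table 1).

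**Assumptions.** The document gives no practice gain L, so 0.2, 0.5 and 1.0 SPPB points are used. The SD of change is taken as 1.2 to 1.5, borrowed from the sample size statement.

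**1. The plan's own figure.** Read 10% as 10% of the 12-point scale, i.e. 1.2 points, two-sided. Then n per group = 2 × [SD × (1.960 + 0.842) / 1.2]².
- SD 1.2: 15.7, rounded up to 16.
- SD 1.5: 24.5, rounded up to 25.

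This reproduces the stated 16 to 25, so 1.2 points serves as the yardstick. The sample size does not depend on how baseline is defined.

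**2. Practice left in the change.** Let baseline 1 = m, baseline 2 = m + L, and follow-up = m + L + E with no treatment effect, where E is any further practice gain.
- Change from the mean: (m + L + E) − (m + L/2) = L/2 + E.
- Change from baseline 2: E.

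If learning is complete at the second test and is retained, E = 0 and averaging leaves exactly L/2.

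**3. Size within the NHD group.** For a one-sample t test with n = 25 and no true change, the noncentrality is (L/2) / (SD/√25) with 24 degrees of freedom.

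| Assumed L | Bias L/2 | Share of 1.2 | Noncentrality, SD 1.2 / 1.5 | Error rate, SD 1.2 / 1.5 |
|---|---|---|---|---|
| 0.2 | 0.10 | 8% | 0.42 / 0.33 | 6.9% / 6.2% |
| 0.5 | 0.25 | 21% | 1.04 / 0.83 | 17.0% / 12.6% |
| 1.0 | 0.50 | 42% | 2.08 / 1.67 | 51.6% / 36.0% |

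If the third test adds a further L/2, the residual against the mean doubles to 0.20, 0.50 and 1.00 points. Against baseline 2 it is 0.10, 0.25 and 0.50.

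**4. Size between groups.** Controls follow the same schedule, so the bias in the difference of changes is (L_NHD − L_CHD)/2, where CHD is conventional haemodialysis. With equal learning it is 0. With 1.0 against 0.5 it is 0.25 points.

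**5. Precision of the alternatives**, one follow-up occasion, compound symmetry with correlation rho, in units of (1 − rho) × SD².
- Mean baseline: per-patient variance of change 1.5, so 1.5/25 = 0.06 for the NHD mean.
- Practice term shared by both groups: baseline 2 is estimated as the baseline mean plus half the pooled practice estimate. This adds ¼ × 2/50 = 0.01, giving 0.07. The standard error ratio is √(0.07/0.06) = 1.08. In the between-group contrast the shared term cancels, so nothing is lost.
- Group-specific term, or baseline 2 alone: 2/25 = 0.08. The ratio is √(0.08/0.06) = 1.155.

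**6. What a shared term leaves under unequal learning.** The between-group bias stays (L_NHD − L_CHD)/2. The within-NHD bias becomes L_NHD/2 − (L_NHD + L_CHD)/4 = (L_NHD − L_CHD)/4. For 1.0 against 0.5 these are 0.25 and 0.125 points.

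**The case against.** The strongest reply is that the plan has a second safeguard and names it: the Discussion says the control group is there "to account for changes over time and a possible learning effect of certain tests". The Abstract and the closing paragraph frame the aim as NHD against CHD, the sample size is per group, and Statistical analyses defines no within-group test. All of this stands. If both groups learn equally, the between-group estimate is unbiased whichever baseline is used.

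A reader might go further and infer that the between-group result is biased too, because the Discussion expects NHD patients to be keen to follow their own progress and controls less so. The document does not support this. Those remarks concern willingness to take part, not practice gains, and both groups are still on CHD at both baselines. Equal learning is not assured in groups formed by patient preference, but nothing in the text shows it to be unequal.

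Three further points have weight. Averaging lowers baseline noise (1.5 against 2.0 in the units above), although the text gives learning, not precision, as the reason for the duplicate. Comparing the two baselines would let learning be checked, which is one reading of ruling it out, but the plan does not say that this comparison will change the analysis. Finally, the size rests on an assumed L: at 0.2 points the error rate hardly moves, and 1.0 point is 83% of the 1.2-point target. Taking the better of two gait trials and of two grip trials limits practice in part; chair stands, balance and the six-minute walk have no such repeat.

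**Conclusion.** The point holds as a moderate one. For SPPB, six-minute walk and handgrip strength, the averaging rule does not achieve the purpose stated in the sentence before it. Change from baseline keeps half of any retained practice gain, and more if learning continues after the second test. This biases the within-NHD comparison with baseline named in the Discussion, by 0.10 to 0.50 SPPB points over the assumed range of L. The corresponding error rate runs from 6-7% to 36-52% instead of 5%.

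These figures rest on the assumed L, on an SD of change of 1.2 to 1.5, and on a simple test at one follow-up occasion. It would be wrong to conclude that the NHD-versus-CHD result is invalid: its bias is (L_NHD − L_CHD)/2, which is zero with equal learning. The trial can answer its main question without this change, so the point is not a must-fix. Measures with no practice effect, such as weight and laboratory values, are not affected. Nor are those with a single baseline in Table 1 (DXA, dietary intake, FGF-23 and sclerostin).

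**What to change.** For SPPB, six-minute walk and handgrip strength only:

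- Enter baseline 1 and baseline 2 as separate occasions in the mixed model, with a practice term for baseline 1 versus 2. Estimate within-group change against baseline 2.
- Report the baseline 1-to-2 change by group, so that readers can see how large learning was and whether it differed.
- Let the practice term be shared by both groups in the main model. Under compound symmetry this costs nothing for the between-group contrast and about 8% on the standard error of within-NHD change. It does not correct unequal learning.
- As a sensitivity analysis, use a group-specific practice term or baseline 2 alone. Either corrects unequal learning if it is complete by the second test. Baseline 2 alone raises the SD of simple change by about 15%.
- State that the main inference rests on the between-group contrast.

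Keep the mean of duplicate baselines for measures without a practice effect, and give precision as its purpose. The change is to the analysis text only; it needs no new visits, data or patients.
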